#### Cost-effectiveness analysis (CEA)

##### General considerations

Alongside the randomised clinical trial an economic study will be performed. The economic evaluation will be set up as a cost-effectiveness analysis (CEA). The CEA focuses on the possible gained benefits of ESS in addition to drug treatment versus drug treatment alone and the related health care costs. The economic evaluation will be performed from a societal point of view.

##### Patient outcomes

The SNOT-22 will be measured to evaluate impact of both treatments. This will be used as endpoint in the economic evaluation. The cost-effectiveness of the interventions will be compared by assessing cost per Quality-adjusted Life Year (QALY), calculated from the health utility scores obtained with the *EQ-5D-5L*.

##### Cost analysis

Costs will be primarily assessed by the intervention study (and not the additional costs of underlying comorbid diseases). The time horizon of this cost analysis will be limited to 12-month follow-up. With this time horizon no discounting of costs and effects will be performed. The societal perspective captures the value of all resources used. Costs associated with treatment from a long-term perspective will be estimated and incorporated in a scenario analysis. Subgroup analyses will be done. Overall costs will be compared across the treatment groups and, where relevant, differences will be calculated, inclusive of 95% confidence intervals. Incremental cost-effectiveness ratios (iCERs) will be calculated.

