### Study design

The PolypESS is an investigator-initiated, prospective, open, national, multicentre randomised controlled trial investigating the (cost-)effectiveness of ESS in patients suffering from CRSwNP. Suitable patients will be randomised into two treatment groups. In the first group patients will undergo ESS in addition to medication, in the second group patients will receive an intensified drug treatment only. Total follow-up is 24 months for all included consecutive patients. Otorhinolaryngologists in the participating centres are asked to recruit patients. Any patient who meets the inclusion criteria (described in detail below in ‘Study population’ section) will be informed about the trial and asked to participate. The coordinating trial centre (Academic Medical Centre, Amsterdam, The Netherlands) will contact patients who have expressed interest in the trial. The study team member will provide detailed written and oral information about the trial and answer any questions. If patients agree to participate, inclusion and exclusion criteria will be checked and a baseline visit will be scheduled. Potential participants have sufficient time before they give their final consent to participate in the trial. If patients decline participation, known clinical data on disease-specific HRQOL and objective signs of disease are used to evaluate whether the findings of the consecutive sampling are generalisable to the target population. The trial reporting is according to the CONsolidated Standards of Reporting Trials (CONSORT) guidelines and the CONSORT extension for nonpharmacological interventions (Fig. 1) [14, 15]. The Standard Protocol Items: Recommendations for Interventional Trials (SPIRIT) 2013 Checklist: ‘Recommended items to address in a clinical trial protocol and related documents’, can be found in Additional file 1. The SPIRIT participant schedule is shown in Table 1.

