**Fig. 1 Fig1:**
[figure not shown]
CONsolidated Standards of Reporting Trials (CONSORT) flow diagram of PolypESS study (ESS, endoscopic sinus surgery)

**Table 1 Tab1:** Standard Protocol Items: Recommendations for Interventional Trials (SPIRIT) schedule patient enrolment, interventions and assessments

	Visit -2	Visit -1	Visit 0	Visit 1	Visit 2	Visit 3	Telephone consult	Visit 4
Timepoints	<10 wks	<6 wks		3 months	6 months	12 months	18 months	24 months
ENT-surgeons asks patient to participate	x							
Informed Consent		x						
Demographic Data		x						
Medical History including earlier sinus surgery		x						
Inclusion Criteria		x						
Exclusion criteria		x						
Randomisation		x						
ESS or intensify medical treatment based on randomisation			x					
Vital Signs and bodyweight		x						
Symptoms		x		x	x	x	x	x
Disease specific HRQOL and symptoms (SNOT-22)		x		x	x	x	x	x
Generic HRQOL (EQ-5D-5L)		x		x	x	x	x	x
Endoscopic assessment of the nose		x		x	x	x		x
Olfactory function (Sniffin’ Sticks)		x		x	x	x		x
Nasal obstruction (PNIF)		x		x	x	x		x
Daily records cards (DRC)		x		x	x	x	x	x
CRS disease control		x		x	x	x		x
Asthma control		x		x	x	x	x	x
Healthcare resource use				x	x	x	x	x
Adverse effects				x	x	x	x	x
CT scan (Lund-Mackay score)		x						
Surgical report			x					
Laboratory tests, pregnancy test		x						
Skin Prick test (if done in the last year, results are recorded)		x						

*Wks* weeks, *HRQOL* health-related quality of life, *SNOT-22* sinonasal outcome test 22, *EQ-5D-5L* EuroQol-5D-5L questionnaire, *PNIF* peak nasal inspiratory flow

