#### Secondary study outcomes

Clinical outcome data will be collected at 3, 6, 12, 18 and 24 months after start of treatment. All measurements are performed by an adequately trained medical researcher and research nurses. All measurements are carried out according to protocol procedures and defined standard operating procedures.

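### The cost-effectiveness analysis is limited to 12 months and no 24-month trial-based analysis is stated, although utilities and resource use are scheduled to 24 months

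*Protocol article*

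**What the plan says.** In the Protocol article, under Cost-effectiveness analysis (CEA), the Cost analysis subsection states: "The time horizon of this cost analysis will be limited to 12-month follow-up". It continues: "With this time horizon no discounting of costs and effects will be performed". The limit therefore governs effects as well as costs. For the longer term the same paragraph offers this: "Costs associated with treatment from a long-term perspective will be estimated and incorporated in a scenario analysis". The Patient outcomes subsection makes cost per QALY, from EQ-5D-5L utilities, the measure of comparison.

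The data collection runs longer. Study design: "Total follow-up is 24 months for all included consecutive patients". Secondary study outcomes: "Clinical outcome data will be collected at 3, 6, 12, 18 and 24 months after start of treatment". In Table 1 the row "Healthcare resource use" is marked at 3, 6, 12, 18 and 24 months, and the EQ-5D-5L row at the same times plus enrolment. Study objectives lists generic quality of life over 12–24 months among the key secondary aims.

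**The concern.** The two arms spend money at different times. According to Interventions, surgery is offered no later than six weeks after randomisation, and Measurements counts it as a direct medical cost, so in the ESS arm it falls almost wholly in year 1. Benefit, medication and exacerbations continue into year 2 in both arms. So may revision surgery, and surgery in drug-arm patients, all of whom were selected as surgical candidates. A 12-month window counts the initial operation in full and none of these later items.

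The article itself treats repeat surgery as important. The Background cites a UK survey in which 20% of respondents with polyps had had multiple operations, and the budget impact analysis needs reintervention data. The Discussion also names as a limitation of an earlier Markov evaluation that it was not done alongside a randomised trial. Here randomised second-year data are scheduled, but the stated plan puts them in no cost-per-QALY comparison. At stake is whether the trial can say from its own data if an early surgical cost is worth paying over two years.

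**Working it through.** The document gives no cost, utility or iCER, so there is no stated figure to reproduce. What follows shows how far a 12-month result could lie from a 24-month one. The effect paths and year-2 costs are assumptions.

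**Inputs from the document:** measurement times of 0 (enrolment), 3, 6, 12, 18 and 24 months (Table 1); horizon 12 months; follow-up 24 months. The horizon covers 12/24 = half of the follow-up time.

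**Assumed:** a between-arm utility difference v that starts at 0 and is expressed as a fraction of its full value; no discounting; positive QALY gain and positive incremental cost at both horizons.

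**Formulas**
- QALY gain to time T: A(T) = sum over intervals of (v at start + v at end)/2 × interval length in years.
- Share captured by 12 months = A(12)/A(24).
- With year-1 incremental cost C and year-2 incremental cost kC: iCER(12) = C/A(12) and iCER(24) = (1 + k)C/A(24). The ratio iCER(24)/iCER(12) = (1 + k) × A(12)/A(24).

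**Worked case: full gain at 3 months, sustained**
- A(12) = 0.5 × 0.25 + 1 × 0.25 + 1 × 0.5 = 0.875.
- A(24) = 0.875 + 1 × 0.5 + 1 × 0.5 = 1.875.
- Share = 0.875/1.875 = 0.467, about 47%.
- Ratio for k = −0.2, 0 and +0.2: 0.37, 0.47 and 0.56.

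**All paths**

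| Assumed v at 0, 3, 6, 12, 18, 24 months | A(12) | A(24) | Share | Ratio at k = −0.2 / 0 / +0.2 |
|---|---|---|---|---|
| Slow build, then sustained: 0, 0.25, 0.5, 1, 1, 1 | 0.500 | 1.500 | 33% | 0.27 / 0.33 / 0.40 |
| Sustained: 0, 1, 1, 1, 1, 1 | 0.875 | 1.875 | 47% | 0.37 / 0.47 / 0.56 |
| Wanes to half: 0, 1, 1, 1, 0.75, 0.5 | 0.875 | 1.625 | 54% | 0.43 / 0.54 / 0.65 |
| Wanes to zero at 24: 0, 1, 1, 1, 0.5, 0 | 0.875 | 1.375 | 64% | 0.51 / 0.64 / 0.76 |
| Linear fall from month 3 to zero at 24: 0, 1, 18/21, 12/21, 6/21, 0 | 0.714 | 1.000 | 71% | 0.57 / 0.71 / 0.86 |
| Gone by 18: 0, 1, 1, 1, 0, 0 | 0.875 | 1.125 | 78% | 0.62 / 0.78 / 0.93 |
| Gone by 12: 0, 1, 0.5, 0, 0, 0 | 0.438 | 0.438 | 100% | 0.80 / 1.00 / 1.20 |

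**Direction.** The 24-month iCER exceeds the 12-month one when k > A(24)/A(12) − 1. That threshold is 1.875/0.875 − 1 = 1.14 for a sustained gain, 1.125/0.875 − 1 = 0.29 if the gain is gone by 18 months, and 0 if it is gone by 12. The sign thus depends on how the year-2 effect compares with year-2 costs, and the document gives neither.

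**The case against.** The 12-month horizon fits the design. It matches the primary SNOT-22 time point, and omitting discounting is consistent with one year. Year-2 EQ-5D-5L data have another stated use, the long-term quality-of-life comparison. By 24 months there will be more missing data, and more crossover to blur an intention-to-treat contrast. All of this stands. It justifies a 12-month analysis, and it makes moving the base case to 24 months a debatable trade-off that this point does not require. It does not justify having no 24-month analysis, because QALYs and costs accumulate over time.

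The article also plans scenario and sensitivity analyses. A reader might infer that observed second-year data are being replaced by modelling assumptions. The text does not say so: it says only that long-term costs will be estimated, and does not exclude using the 18- and 24-month data. But that sentence names costs and not QALYs. The other scenario analysis, under Statistical analysis, concerns implementation of a screening strategy, which this trial does not test. Neither is a trial-based 24-month cost-per-QALY comparison.

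Finally, the article is a condensed account and promises a detailed analysis plan before database lock. A 24-month analysis could be specified there. The 12-month limit, however, is stated outright, so the point does not rest on silence.

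**Conclusion.** The point holds as a weakness in an analysis choice. It is neither a contradiction nor an arithmetical error. The stated economic evaluation uses half of the scheduled follow-up time, and its iCER may differ materially from a 24-month one. With no year-2 incremental cost, the 24-month iCER would be about 0.47 times the 12-month value if the gain is reached at 3 months and sustained, and 0.33 to 1.0 times across the assumed paths. Letting year-2 incremental cost be 20% of year 1 in either direction widens this to 0.27 to 1.20. These figures are illustrations, undiscounted, and rest on assumed paths.

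Two stronger readings are tempting and unsupported. One is that half of the benefit is discarded, so that the iCER doubles. Half is the share of time; the share of benefit is near half only if the gain is roughly sustained, and doubling also needs an immediate, constant gain and no net cost in year 2. The other is that the plan is biased against surgery. That follows if the gain persists without large extra year-2 costs, but an early fade or frequent revision surgery would turn the error the other way. This uncertainty is a reason to analyse the second year.

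**What to change.** Before database lock, in the promised analysis plan or by amendment:

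- Keep the 12-month analysis if wanted, and pre-specify beside it a within-trial 24-month cost-per-QALY analysis that uses the observed 18- and 24-month EQ-5D-5L and resource-use data.
- Discount second-year costs and effects at a stated rate. The article cites the Dutch costing guidelines only for prices, so the rate needs its own statement.
- State how missing 18- and 24-month data will be handled.
- Limit the no-discounting sentence to the 12-month analysis.
- Start any long-term extrapolation from 24 months.

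No new data collection is needed. The cost is some extra analysis work, and a 24-month result that carries more missing data and more crossover than the 12-month one. Reporting the two together lets readers weigh that.

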##### Measurements

The prospective cost evaluation will primarily focus on health care utilisation (direct medical costs), travel expenses (direct nonmedical costs) and lost productivity (indirect costs) due to absence from work or decreased performance at work (productivity loss). The direct medical costs include the costs of all procedures associated with both treatment strategies (e.g. doctor’s visits, medication, hospital admissions and surgical interventions, sinus CT, endoscopy and exacerbations).

Out-of-pocket expenses include additional over-the-counter drugs and travel costs. Additional costs as a result of comorbid conditions (e.g. asthma) will be excluded.

In the base case analysis, indirect costs (based on lost productivity) will be calculated using the friction cost method. Productivity losses will be estimated based on data concerning absence from work. Health service resource use and costs of both treatment strategies will be measured from a health service and societal perspective. Protocol-driven costs will be excluded.

##### Unit costs

Costs are defined as the volumes of used resources multiplied by calculated unit prices. For the valuation of health care utilisation, standard prices published in the Dutch costing guidelines and market prices will be used [24]. Standard guideline prices will be used for all diagnostic interventions, hospital admissions, post-operative care, outpatient visits and travelling.

##### Statistical analysis

As most volumes of resource utilisation follow a skewed distribution, differences between the two groups will be statistically evaluated with bias-corrected bootstrap analysis. An iCER will be calculated, with the observed HRQOL as effect parameter.

The economic analysis will be expanded with a scenario-analysis to extrapolate the consequences of implementation and actual performance of the screening strategy in the targeted population. In sensitivity analysis the validity of the developed scenarios is evaluated. Uncertainty will be addressed by means of bootstrapping.

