### Baseline measurements

On the day of enrolment, patients will undergo the same HRQOL and objective evaluation, including the SNOT-22, the EuroQol-5D-5L questionnaire (EQ-5D-5L, the EuroQol Group) and nasal endoscopy, that will be used after treatment (see “Outcomes” section). Clinical data is collected by the enrolling medical researcher and focuses on the (severity of) patient-reported symptoms, previous clinical examinations, previous sinonasal surgery, previous conservative treatment and complete medical history. Demographic variables include age, gender, ethnicity, marital status, family situation and highest level of education. Additional study information includes the presence or absence of asthma, acetylsalicylic acid (ASA) intolerance, allergy, occupational exposure, smoking habits and alcohol consumption. Objective measurements recorded are baseline height, weight, blood pressure, resting heart rate, total IgE, serum eosinophil level and computed tomography (CT) scores using the Lund-Mackay scoring system. This system uses a 0–1–2 score dependent upon absent, partial or complete opacification, respectively, of each individual sinus and the ostiomeatal complex, contributing to a maximum score of 12 per side. The total score of the two sides can reach a maximal 24 points [16]. A urine pregnancy test will be performed in female patients with childbearing potential if in doubt of pregnancy.

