### Statistical methods

#### Primary data analysis

Results will be based on the intention-to-treat method. In addition, per-protocol analysis, including only patients who adhered completely to the clinical trial instructions and treatment specified in the protocol, will also be performed to check the robustness of results. Continuous normally distributed variables will be expressed by their mean and standard deviation or, when not normally distributed, as medians and their interquartile ranges. Categorical variables will be expressed as counts (*n*) and percentages (%). Effects on HRQOL, nasal endoscopy and symptom score will be calculated as mean differences with 95% confidence intervals. HRQOL, short- and long-term effects will be additionally evaluated at 3, 6, 12, 18 and 24 months’ follow-up, respectively. It is expected that randomisation will balance patients’ baseline characteristics. However, if imbalances occur between groups that are related to possible effect modification, subgroup analyses will be performed according to the indication for surgery.

A further detailed statistical analysis plan will be developed and reported by the chief investigators prior to the database being locked at the end of follow-up for final analysis.

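### The cost-per-QALY ratio reads as using a QALY difference unadjusted for baseline EQ-5D-5L utility; naming the QALY and adjusting it would gain precision at no cost

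*Protocol article*

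**What the plan says.** All references are to the protocol article.

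- *Cost-effectiveness analysis, Statistical analysis*: "An iCER will be calculated, with the observed HRQOL as effect parameter". Uncertainty is to be handled by bootstrapping.
- *Cost-effectiveness analysis, Patient outcomes*: "The cost-effectiveness of the interventions will be compared by assessing cost per Quality-adjusted Life Year (QALY), calculated from the health utility scores obtained with the" (the sentence ends by naming the EQ-5D-5L). The same paragraph says of the SNOT-22: "This will be used as endpoint in the economic evaluation".
- *Cost-effectiveness analysis, Cost analysis*: "The time horizon of this cost analysis will be limited to 12-month follow-up".
- *Primary data analysis*: "Effects on HRQOL, nasal endoscopy and symptom score will be calculated as mean differences with 95% confidence intervals". This section expects randomisation to give balance. If an imbalance linked to possible effect modification appears, it offers subgroup analyses by indication for surgery. It also promises a more detailed analysis plan before database lock.
- *Baseline measurements*: the enrolment assessment is described as "including the SNOT-22, the EuroQol-5D-5L questionnaire (EQ-5D-5L, the EuroQol Group) and nasal endoscopy, that will be used after treatment". Table 1 repeats the EQ-5D-5L at 3, 6, 12, 18 and 24 months.
- *Randomisation*: blocks of 6, stratified by centre only.

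No section mentions adjusting utilities, QALYs or costs for their baseline values. No section says that they will be left unadjusted.

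**The concern.** Baseline utility matters in two ways when a QALY is an area under the utility curve. It is the first point of the curve, and it predicts the later points. A difference between arms before treatment starts cannot be a treatment effect, yet an unadjusted comparison carries part of it into the QALY difference. That difference is the denominator of the ratio on which the economic conclusion rests.

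Neither safeguard in the text addresses this. Stratifying by centre does not balance utility. Subgroup analyses by surgical indication do not remove a utility difference within a subgroup, and they are triggered only by imbalances related to effect modification. The variable that would address it is already collected and has no stated use in the analysis.

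The effect parameter is also loosely named. Cost per QALY needs the EQ-5D-5L, but the article makes the SNOT-22 an economic endpoint too, so the sentence on the ratio can be read either way.

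**Working it through.** **The plan's own figure.** The sample size rests on a SNOT-22 difference of 8.9, SD 20.0, 5% significance, 90% power and 10% loss. Assuming a two-sided test and 1:1 allocation, n per arm = 2 × (1.960 + 1.282)² × (20/8.9)² = 106.1, so 107. The total is 214, and 214/0.9 = 237.8, so 238. The stated 238 is reproduced. It concerns the SNOT-22 and is used here only to supply 107 completers per arm.

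**Assumptions, because the document gives none of these.** The QALY is the trapezoid area under EQ-5D-5L utilities at 0, 3, 6 and 12 months. The utility SD is equal at all visits, between 0.15 and 0.25. A common correlation ρ of 0.3, 0.5 or 0.7 holds between all visits.

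**Weights.** The intervals are 0.25, 0.25 and 0.5 years, so the weights are 0.125, 0.25, 0.375 and 0.25. They sum to 1 and their squares sum to 0.28125.

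**Formulas.**

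- Carry-over per unit of baseline difference (slope of QALY on baseline) = 0.125 + 0.875ρ
- Var(QALY)/SD² = 0.28125 + 0.71875ρ
- R² = slope² / (Var/SD²)
- Adjusted SE / unadjusted SE = √(1 − R²)
- Unadjusted SE = SD × √(Var/SD² × 2/107)

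| ρ | Slope | Var/SD² | R² | SE ratio | SE at SD 0.20, unadjusted → adjusted |
|---|---|---|---|---|---|
| 0.3 | 0.39 | 0.497 | 0.30 | 0.84 | 0.019 → 0.016 |
| 0.5 | 0.56 | 0.641 | 0.49 | 0.71 | 0.022 → 0.016 |
| 0.7 | 0.74 | 0.784 | 0.69 | 0.55 | 0.024 → 0.013 |

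Under a common correlation the interval therefore narrows by 16%, 29% or 45%.

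**Less favourable correlations.** Pre-treatment utility may correlate with follow-up less strongly than follow-up visits correlate with each other. Take 0.3 for baseline to follow-up and 0.6 between follow-up visits. The three follow-up weights sum to 0.875, with squares summing to 0.2656.

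- Var/SD² = 0.125² + 2 × 0.125 × 0.875 × 0.3 + 0.2656 + 0.6 × (0.875² − 0.2656) = 0.647
- Slope = 0.125 + 0.875 × 0.3 = 0.3875, and its square is 0.150
- R² = 0.150/0.647 = 0.23, and the SE ratio = √0.77 = 0.88

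The interval then narrows by about 12%, so 16% is not a lower bound.

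**Size of a chance imbalance.** The SE of the baseline utility difference is SD × √(2/107): 0.021, 0.027 and 0.034 at SD 0.15, 0.20 and 0.25. At SD 0.20 and ρ 0.5, a one-standard-error imbalance moves the QALY difference by 0.5625 × 0.027 = 0.015. Over SD 0.15 to 0.25 and ρ 0.3 to 0.7 the range is 0.008 to 0.025.

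For a baseline difference of 0.03, the shift is 0.012, 0.017 or 0.022 QALY at ρ 0.3, 0.5 or 0.7. Only 0.125 × 0.03 = 0.004 comes from the baseline weight itself. The rest comes through the correlation with later utilities.

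**The case against.** The strongest reply is that the article never commits to an unadjusted ratio. In the quoted sentence, observed may simply mean trial data, in contrast to the extrapolated scenarios in the next paragraph. The mean-difference sentence stands under the clinical analysis. The bias-corrected bootstrap is introduced for skewed resource volumes, so it says little about the QALY, and bootstrapping for uncertainty is fully compatible with a regression refitted in each resample. Covariates are commonly settled in an analysis plan, and one is promised.

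Most of this stands, and it limits the point to an improvement. It does not dispose of it. A later plan that follows the article would start from an unnamed instrument, a mean difference and an imbalance remedy that cannot correct a utility difference.

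A reader might infer more than the document supports:

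- *That the whole baseline difference is counted as QALY gain or loss.* Carry-over is partial, 0.39 to 0.74 under the assumptions used.
- *That the unadjusted ratio is invalid.* The unadjusted QALY difference is unbiased over randomisations, and a bootstrap interval reflects the variability due to chance imbalance. What remains is lost precision, and bias conditional on the imbalance that actually occurs.
- *That the imbalance could reverse the sign of the ratio, or that adjustment buys a stated amount of power.* The article gives no expected QALY difference to set against 0.015, and it plans no powered QALY test.

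**Conclusion.** The point holds as a free improvement, not as a demonstrated error. Read most directly, the article leads to a 12-month QALY difference without baseline adjustment, although baseline EQ-5D-5L is available.

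The consequence is partial carry-over of any chance utility imbalance and a confidence interval that adjustment would narrow by about 12% to 45%. Both sizes depend on assumptions that the document neither gives nor contradicts: the area-under-the-curve QALY and the visit correlations. The absolute shifts in QALYs also depend on the assumed utility SD and on 107 completers per arm. The direction of the gain depends only on baseline utility predicting later utility. Its size should be treated as illustrative.

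**What to change.** In *Cost-effectiveness analysis, Statistical analysis*, or in the analysis plan before database lock:

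1. State that the effect parameter for cost per QALY is the 12-month QALY from the EQ-5D-5L. If a ratio based on the SNOT-22 is also intended, name it separately.
2. Estimate the incremental QALY as the treatment coefficient from a linear regression of the 12-month QALY on arm and baseline EQ-5D-5L utility.
3. Refit that regression in every bootstrap sample, resampling each patient's costs and QALYs together.
4. Report the unadjusted ratio as a sensitivity analysis.

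The cost is a sentence or two of text and one regression inside the bootstrap already planned. It needs no additional data, visits or patients, and the sample size of 238 is unaffected.
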